**Methods:**

In this randomized controlled trial, 300 patients diagnosed with TMD will be grouped into one of the three interventional groups based on the type of their edentulous state. The interventional groups are (1) partially edentulous arch: Kennedy Class I and II (prosthetic rehabilitation without splint); (2) partially edentulous arch: Kennedy Class III and IV (prosthetic rehabilitation with a splint); and (3) completely edentulous arches (prosthetic rehabilitation without splint). All three of the mentioned interventional groups have corresponding control groups that will receive symptomatic treatment and comprehensive counseling. The measured primary outcomes are pain and electromyogram, and the secondary outcomes include pain drawing, Graded Chronic Pain Scale, Jaw Functional Limitation Scale, Oral Behaviours Checklist, depression, physical symptoms, and anxiety. The outcome measurements will be recorded at baseline and at the end of 24 hours, 7 days, 28 days, and 3 months.

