### Interventions

The participants will be grouped into 3 interventional and 3 control groups based on their state of edentulism (Figure 1; higher-resolution version in Multimedia Appendix 1). The interventional groups are:

Partially edentulous arch—Kennedy Class I and Class II: Kennedy Class I describes a patient who has edentulous areas bilaterally, posterior to the remaining natural teeth. Kennedy Class II describes a patient who has a one-sided edentulous area, posterior to the remaining natural teeth. The participants of this group will receive mouth preparation, prosthetic rehabilitation with removable partial denture, and comprehensive counseling (n=50).Partially edentulous arch—Kennedy Class III and Class IV: In Class III the edentulous area has teeth located both anteriorly and posteriorly to it. In Class IV, there will be a single but bilateral (crossing the midline) edentulous area located to the anterior of the remaining natural teeth. The participants of this group will receive mouth preparation and prosthetic rehabilitation with removable partial denture followed by management with stabilization splint and comprehensive counseling (n=50).Completely edentulous arches: The participants of this group will receive prosthetic rehabilitation with removable complete denture and comprehensive counseling (n=50).

Each of the 3 mentioned interventional groups will have their corresponding control groups with 50 participants in each control group. The participants in all the 3 control groups will receive symptomatic treatment and comprehensive counseling.

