### Sample Size

The activity of masticatory muscle (mean and SD) while chewing, estimated by EMG, reflects the TMD in a patient [35]. With a power of 80%, alpha error of .05, and effect size of 0.77, the minimum sample size estimated for each group was 22. Considering attrition and the inclusion of various variables (edentulousness location, etc), we increased the sample to 50 for each interventional group. The sample size of 50 will have a minimum of 20 patients with edentulous maxilla and 20 patients with edentulous mandible for intervention groups 1 and 2. The total sample size for the study is 300 with 150 for the interventional group and 150 for the control group. Please refer to Table 2 for the sample breakdown.

**Table 2 table2:** Sample size breakdown.

			Group 1: removable partial denture, n		Group 2: removable partial denture with stabilization splint, n		Group 3: removable complete denture, n		Total, n
**Intervention**			50		50		50		150
	Patients with edentulous maxilla	20		20		20			
	Patients with edentulous mandible	20		20		20			
	Total	40		40		40			
	Females	20		20		20			
	Males	20		20		20			
	Total	40		40		40			
**Control**			50		50		50		150
	Patients with edentulous maxilla	20		20		20			
	Patients with edentulous mandible	20		20		20			
	Total	40		40		40			
	Females	20		20		20			
	Males	20		20		20			
	Total	40		40		40			
Sample per group			100		100		100		300

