**Subgroup analysis**							
	Effectiveness of reduction of pain: between group 1, group 2, and group 3	Intervention improved outcome from baseline to 12 months		Per person reduction of VAS score and GCPS (proportion or mean)		Regression methods with appropriate interaction term	
	Between posterior teeth rehabilitation vs anterior teeth rehabilitation	Number of teeth affects effectiveness of outcome		Per person reduction of VAS score and GCPS (proportion or mean)		Chi-square methods	
	Upper vs lower teeth	Position of edentulism affects the effectiveness outcome		Per person reduction of VAS score and GCPS (proportion or mean)		Chi-square methods	
	Duration of edentulism	Duration of edentulism affects pain outcome		Per person reduction of VAS score and GCPS (proportion or mean)		Chi-square methods	
	Number of quadrants	Number of quadrants affects the effectiveness outcome		Per person reduction of VAS score and GCPS (proportion or mean)		Chi-square methods	

^a^In all analyses, results will be expressed as coefficient, SEs, corresponding 95%, and associated *P* values. Goodness of fit will be assessed by examining the residuals for model assumptions and chi-square tests for goodness of fit.

^b^VAS: visual analog scale.

^c^GCPS: Graded Chronic Pain Scale.

^d^ANOVA: analysis of variance.

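### The upper-versus-lower subgroup row in Table 3 has no level for patients edentulous in both arches, although such patients are eligible

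*Protocol article*

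**What the plan says.** Table 3 (Statistical Methods, subgroup block) has a row for upper versus lower teeth. Its hypothesis is "Position of edentulism affects the effectiveness outcome", its outcome is the per-person reduction in VAS and GCPS, and its method is chi-square.

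The population is described under Study Population, Eligibility Criteria and Interventions. Partially and fully edentulous people are recruited, and no inclusion or exclusion criterion restricts tooth loss to one jaw. Group 3 is described as "Completely edentulous arches: The participants of this group will receive prosthetic rehabilitation with removable complete denture and comprehensive counseling", and in the abstract as "completely edentulous arches (prosthetic rehabilitation without splint". The article does not say whether one arch or both must be edentulous.

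Sample Size asks for "a minimum of 20 patients with edentulous maxilla and 20 patients with edentulous mandible for intervention groups 1 and 2". Table 2 goes further. It shows 20 maxilla and 20 mandible patients, subtotal 40, in every cell of 50, including both Group 3 cells. It has no row for both arches and does not say where the other 10 in each cell belong.

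**The concern.** A chi-square test comparing two levels needs each patient in exactly one of them. VAS and GCPS give one value per patient and cannot be divided between jaws. A patient edentulous in both arches therefore has no place in the row as written. The protocol implies that such patients exist: another Table 3 row analyses the number of quadrants involved, and anyone with three or four quadrants involved has both arches involved.

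There is a second weakness in the same row. The hypothesis concerns whether position changes effectiveness, which is a difference between arm effects. A chi-square of response against location compares response between locations. It does not compare the effect of rehabilitation between locations.

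If the coding is left open until the data are in, it could be chosen with outcomes known. The choice affects both the error rate and the number of patients behind the result.

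**Working it through.** **Reproducing the plan's figures.** Table 2 has six cells of 50, and 6 × 50 = 300, which agrees with "The total sample size for the study is 300 with 150 for the interventional group and 150 for the control group". Within each cell 20 + 20 = 40, leaving 50 − 40 = 10 unassigned. Group 3 is 50 + 50 = 100, from the group size in Interventions and "Each of the 3 mentioned interventional groups will have their corresponding control groups with 50 participants in each control group". The minimum of 22 per group (effect size 0.77, 80% power, alpha .05) reproduces as a one-sided t-test (21.56, rounded up to 22); a two-sided test gives 28. That calculation concerns EMG and is not used below.

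**How many patients could be affected in both arches.** The article gives no number, so these are assumptions:

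- (a) Table 2's maxilla and mandible rows are exclusive and filled: at most 10 × 6 = 60, and 60/300 = 20%. Of these, 20 are in Group 3.
- (b) All of Group 3 is edentulous in both arches and Groups 1 and 2 are single-arch: 100/300 = 33%.
- (c) As (b), plus the 10 unassigned in each of the four Group 1 and 2 cells: (100 + 40)/300 = 47%.

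**If both-arch patients were entered in both levels.** Let s be the shared patients and u = (300 − s)/2 the single-arch patients per level, assuming an equal split. Each level then has n = u + s entries.

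- Dilution: the shared patients add the same amount to both levels, so the observed difference is u/n times the true single-arch difference.
- Null rejection rate: the difference has true variance 2u·p(1−p)/n², but the test assumes 2p(1−p)/n. The ratio is u/n, so the nominal 5% test rejects with probability 2[1 − Φ(1.96/√(u/n))].

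| Reading | s | u | n | u/n | Null rejection rate |
|---|---|---|---|---|---|
| (a) | 60 | 120 | 180 | 0.67 | 1.6% |
| (b) | 100 | 100 | 200 | 0.50 | 0.6% |
| (c) | 140 | 80 | 220 | 0.36 | 0.1% |

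Simulation with 200,000 replicates and 50% response gives about 1.7%, 0.5% to 0.6%, and 0.1%. With an assumed 60% v 40% response in the single-arch levels and 50% in the shared patients, power under double entry is about 77%, 53% and 24%. Comparing only single-arch patients gives about 87%, 82–83% and 72%.

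**If both-arch patients were left out.** The single-arch patients number 300 − 60 = 240, 300 − 100 = 200 or 300 − 140 = 160. The test is then valid. Only precision falls. For 80% power at two-sided 5%, the detectable standardised difference is (1.96 + 0.84)·√(1/u + 1/u):

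- 300 patients (u = 150): 0.32
- 240 (u = 120): 0.36
- 200 (u = 100): 0.40
- 160 (u = 80): 0.44

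For the arm-by-location interaction, with arms equal within location, the variance term becomes 4/u + 4/u. The detectable values double to 0.65, 0.72, 0.79 and 0.89.

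**The case against.** The strongest reply is that the article never says both-arch patients will be dropped or entered twice. Table 3 is a list of proposed analyses in a condensed article, and a chi-square can take three levels as easily as two. Coding a subgroup factor is often left to an analysis plan, and none is shown here. Double entry, moreover, makes the test conservative, so it would not produce false positives. Omission gives a valid test.

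Much of this stands. A reader might infer that a third of the trial or more will be dropped or counted twice. The documents do not support that. The third assumes that every Group 3 patient is edentulous in both jaws, whereas Table 2 plans 20 maxilla and 20 mandible patients in each Group 3 cell. If those rows are exclusive, the share is at most 20%. A reader might also take a halved contrast and a rejection rate near 0.5% as properties of the plan. They arise only under double entry, which is planned nowhere, and only at the one-third share.

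The reply does not remove the mismatch. The protocol itself names the two levels, the per-person unit and the test, and these do not fit the patients it enrols. Table 2 adds the same two levels as though they were exclusive, and the text and the table disagree on whether the split applies to Group 3. Nor would a third chi-square level make the row a test of whether location modifies the effect of treatment.

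**Conclusion.** The concern holds in a limited form: the levels of this row do not cover the eligible population, and the method does not address the hypothesis beside it. The share without a level is up to 20%, 33% or 47%, depending on how Group 3 and Table 2 are read. These are readings, not bounds, because the article does not say whether Table 2's maxilla and mandible counts may overlap. The cost is either a diluted, conservative test or a valid test on about 240, 200 or 160 patients; the article does not say which. The figures assume an equal upper-lower split and, for the rejection rates, independent responses with equal probability in both levels. The point should be corrected, but it concerns one subgroup row and leaves the primary randomised comparison of pain untouched.

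**What to change.** - Derive one baseline variable with three levels, maxilla only, mandible only and both, and assign each patient once.
- Replace the chi-square in this row with a regression containing group, arm, location and arm-by-location. Table 3 already names regression with an interaction term for the comparison of the three groups.
- Make the upper-versus-lower contrast between the two single-arch levels, report the both-arch level separately, and state how many patients contribute to each.
- State whether Group 3 requires one edentulous arch or both.
- Reconcile the Sample Size text, which gives the 20/20 minimum for intervention groups 1 and 2, with Table 2, which also shows it for Group 3, and say where the remaining 10 in each cell belong.

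The change needs one derived variable from the baseline oral examination and a reworded row. The price is a contrast on fewer than 300 patients if any are affected in both arches, and an interaction test that can detect only large differences (about 0.7 to 0.9 SD under the three readings). The report should say so.

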### Analysis Population and Missing Data

We will report reasons for withdrawal for each randomization group and compare the reasons qualitatively. The effect that any missing data might have on results will be assessed via sensitivity analysis of augmented data sets. Dropouts will be included in the analysis by using multiple imputation methods for missing data. Excluding patients from the analysis who violated the research protocol (did not get their intended treatment) can have significant implications that impact the results and analysis of a study. If the attrition loss is less than 15%, a per protocol analysis will be carried out; otherwise, “intention to treat” will be performed.

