### Blinding

Due to the obvious nature of the treatment, neither the treating dentist or patients are blinded; patients are only randomly allocated to the intervention. However, the data analyst or statistician will be blinded during the statistical process.

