### Data Collection Methods

Each personnel will be trained centrally for the study requirements, standardization of examination and assessment of the outcomes and counselling for adherence, and the eliciting of information from study participants in a uniform reproducible manner. The data to be collected and the procedures to be conducted at each visit will be reviewed in detail. Each of the data collection forms and the nature of the required information will be discussed in detail on an item-by-item basis. Entering data forms, responding to data discrepancy queries, and general information about obtaining research quality data will also be covered during the training session. Once an individual is enrolled or randomized, the study site will make every reasonable effort to follow the individual for the entire study period of 12 months. It is projected that the rate of loss-to-follow-up on an annual basis will be at most 5%.

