### Compliance With Trial Treatment

The follow-up visits of the individual are important for the trial. Compliance to visit the dental clinic at designated intervals is done by telephonic and email reminders to the individuals. If the individual has missed the appointment or wants to reschedule, then it is rescheduled within +/– 2 days. If the individual misses two rescheduled appointments, then it is referred as noncompliance. The individual will be withdrawn from the study. However, if the individual completes 6 months and becomes noncompliant for the next 6 months, the person’s time of participation in the trial will be counted and will be used for analysis.

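### The analysis population is chosen from observed attrition, and the protocol's own projection makes per protocol the analysis that will be done for a superiority question

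*Protocol article*

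**What the plan says.** The rule is in the protocol article, Analysis Population and Missing Data: "If the attrition loss is less than 15%, a per protocol analysis will be carried out"; "otherwise, “intention to treat” will be performed". No other analysis population is named anywhere in the article.

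Two sentences just before it point the other way. One concerns patients who drop out: "Dropouts will be included in the analysis by using multiple imputation methods for missing data". The other says that leaving out patients who violated the protocol "can have significant implications that impact the results and analysis of a study".

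Other sections bear on who would be excluded:

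- Data Collection Methods, on expected loss: "It is projected that the rate of loss-to-follow-up on an annual basis will be at most 5" (per cent).
- Blinding: "neither the treating dentist or patients are blinded", although "the data analyst or statistician will be blinded during the statistical process". Trial Design also describes outcome measurement as blinded.
- Retention: the treating dentist may discontinue a patient at any time for any reason. Noncompliance and protocol deviation are among the listed examples.
- Compliance With Trial Treatment: "If the individual misses two rescheduled appointments, then it is referred as noncompliance. The individual will be withdrawn from the study". A further clause counts the participation of a patient who becomes noncompliant after 6 months.
- Hypothesis: rehabilitation reduces pain compared with no rehabilitation, which is a superiority question.

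**The concern.** Attrition is observed after randomisation and may itself depend on treatment. A rule that reads the analysis set off it makes the estimand depend on a result of the trial. Here the branch that applies at low attrition is the one that gives up the randomised comparison.

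For a superiority question, a per-protocol set compares patients who stayed with their allocated management. In this trial the people who shape that set are unblinded: the patient, who decides whether to attend and continue, and the dentist, who may discontinue participation. The pain score is marked by the patient. If those who leave the set differ in pain, and leave in different numbers or for different reasons in the two arms, the comparison is biased. The blinded analyst cannot repair this, because the selection happens before the data arrive.

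**Working it through.** **1. Which branch applies?** Inputs: N = 300, in three groups of 100 with 50 per arm (Sample Size); threshold 15%; projected loss at most 5% a year.

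- Expected loss: 0.05 × 300 = 15. Threshold: 0.15 × 300 = 45.
- The chance of reaching the threshold is P(X ≥ 0.15N, rounded up) with X binomial(N, p). The article does not say whether attrition is counted overall, per group or per arm, so all three are shown.

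| Counted over | Needed | p = 5% | p = 10% |
|---|---|---|---|
| whole trial, N = 300 | 45 | 6 × 10⁻¹¹ | 0.004 |
| one group, N = 100 | 15 | 0.0001 | 0.07 |
| one arm, N = 50 | 8 | 0.003 | 0.12 |

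On the protocol's projection the intention-to-treat branch is almost never reached. Even at double the projected loss, per protocol remains the likely branch. Over 3 months rather than a year, expected loss would be smaller still.

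**2. How large could the bias be?** The protocol gives no figure, so this is an illustration. Assumptions: no true effect; normal outcomes with SD 1; a fraction f of one arm removed, lowest first, on a score correlated c with the outcome; the other arm intact.

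- Shift = c·φ(z)/(1 − f), where z is the f-quantile of the standard normal.
- f = 0.05: z = −1.645, φ = 0.1031, and 0.1031/0.95 = 0.109. With c = 0.3 to 0.5 the shift is 0.033 to 0.054 SD.
- f = 0.14: z = −1.080, φ = 0.2226, and 0.2226/0.86 = 0.259. The shift is 0.078 to 0.129 SD.
- Standard error = √[v/(n(1 − f)) + 1/n], with λ = φ(z)/(1 − f) and v = 1 − c²λ(λ − z). For f = 0.14, c = 0.5, n = 150: v = 0.913 and SE = √(0.913/129 + 1/150) = 0.117.
- Type I error = Φ(−1.96 + shift/SE) + Φ(−1.96 − shift/SE). In that example shift/SE = 1.10, giving 0.196 + 0.001, or about 20%.

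Simulation agrees with the formula:

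| Per arm | Excluded from one arm | Shift (SD), c = 0.3 to 0.5 | Two-sided type I error |
|---|---|---|---|
| 150 | 5% | 0.03 to 0.06 | 6 to 8% |
| 150 | 14% | 0.08 to 0.13 | about 10 to 20% |
| 50 | 5% (2 patients after rounding) | 0.02 to 0.04 | about 6% |
| 50 | 14% | 0.07 to 0.13 | about 7 to 11% |

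**3. Direction.** Removing the same fraction with the same selectivity from both arms gives a simulated shift within 0.001 SD of zero. Selective removal mainly from the control arm reverses the sign.

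**4. Is 14% an upper limit?** No. The 15% threshold counts attrition. A per-protocol set also drops patients who stayed in follow-up but did not get the intended treatment, and nothing in the rule limits their number.

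**The case against.** The strongest defence has three parts. The protocol never calls per protocol the primary analysis. The analyst is blinded and outcome measurement is described as blinded. And at the projected 5% loss, with moderate selectivity, the illustrated error is only 6 to 8%. The first part does not help, because no other analysis is named for that branch. The second does not reach selection made by patients and dentists. The third is a fair limit on size, but the threshold does not bound per-protocol exclusions, and a modest expected bias is no reason to accept one that costs nothing to avoid.

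A reader might also infer stronger points that the article does not support:

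- *Adherence to the prosthesis is never recorded.* In Table 1 the compliance row is marked at visit 1 only, but a review of the prosthesis is scheduled at every visit. What that review captures is not stated.
- *No patient could meet the 6-month clause.* That is true only on the 3-month visit schedule. Data Collection Methods, Table 3 and Data Monitoring give 12 months, and Participation Timeline gives both. This is an unresolved conflict about follow-up. Nor does the clause say that other patients' data are discarded.
- *Per protocol contradicts multiple imputation.* The article describes violators as patients who did not get their intended treatment, who need not be dropouts, and missing outcomes can be imputed within a per-protocol set. The two plans sit uneasily together. The clear tension is with the warning about exclusions.
- *The rule inflates the benefit of prostheses.* The withdrawal rules apply to both arms. Recruitment enrols patients who have opted for prosthetic rehabilitation, so controls have their own reason to leave.

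**Conclusion.** The point holds. The rule lets a post-randomisation result choose the analysis set, and on the protocol's own projection it replaces the randomised comparison with a per-protocol one. That conclusion needs only the rule and the projected loss.

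The size of the bias is not known from the article. The shifts of 0.03 to 0.13 SD and error rates of about 6 to 20% at 150 per arm rest on one-sided exclusion and a correlation of 0.3 to 0.5, both assumed. Much higher error rates, about 65% at 14% excluded with 150 per arm, appear only if exactly the patients at one extreme of the outcome leave, and only from one arm. They should not be read as what this trial would suffer. The sign of the bias is open.

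**What to change.** In Analysis Population and Missing Data, replace the attrition rule with: *The primary analysis is intention to treat (all randomised patients, in the arm and stratum allocated) with multiple imputation of missing outcomes, whatever the attrition; per protocol is a sensitivity analysis.*

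In Compliance With Trial Treatment, state that patients who miss visits stay in outcome follow-up where they consent, and stay in the analysis. This concerns data collection, not treatment. Reconcile the 6-month clause with the 3-month visit schedule and the 12-month follow-up stated elsewhere.

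The cost is a change of wording, plus the effort of following patients who would otherwise be withdrawn. The sample size need not change. The stated minimum of 22 per group becomes 22/0.85 = 25.9, so 26, after allowing for 15% loss. A two-sided t-test at the same effect size of 0.77 needs 28, which becomes 28/0.85 = 32.9, so 33. Both are below the planned 50. The estimate may move in either direction.
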